## Abstract

**Introduction::**

Post-extubation dysphagia is commonly observed in ICU patients and associated with increased aspiration rates, delayed resumption of oral intake/ malnutrition, prolonged ICU and hospital length of stay, decreased quality of life, and increased mortality. Conventional therapeutic approaches are limited. Pharyngeal electrical stimulation (PES) was previously shown to improve swallowing function and airway safety in severely dysphagic tracheostomised stroke patients.

**Methods::**

In a multi-center, single-blind, 1:1 randomized controlled study, up to 400 (360 evaluable) mixed emergency adult ICU patients with recent extubation following mechanical ventilation and confirmed oropharyngeal dysphagia will be enrolled at investigational academic ICUs. Primary objective is to evaluate the effectiveness of PES in reducing the severity of unsafe swallows. Patients will be randomized to receive PES (or sham) treatment on 3 consecutive days in addition to best supportive care. Primary endpoint is a composite of 2 endpoints with hierarchy based on clinical priorities:

**Discussion::**

This study will evaluate the effects of PES on swallowing safety in critically ill ICU patients post mechanical ventilation with oropharyngeal dysphagia.

## Introduction

1

Oropharyngeal dysphagia, also referred to as dysphagia or “disordered swallowing”, is an abnormality of the swallow physiology (reviewed in^[1]^). It is observed frequently in patients with stroke^[2]^ and additional neurological conditions, head and/or neck cancer,^[3]^ cervical spine surgery,^[4]^ prolonged intubation,^[5,6]^ tracheostomy,^[7,8]^ and/or mechanical ventilation.^[9]^ Although the literature reports a high incidence of dysphagia following endotracheal intubation for more than 48 hours, the reported incidence rate varies widely from to 3% to 83%.^[5,10,11]^ Studies have also shown that prolonged intubation might be a risk factor for dysphagia,^[12,13]^ as artificial airways increase the risk of upper airway injury and concomitant laryngeal pathologies.^[14–16]^ However, causes for “ICU-acquired” dysphagia are multifactorial and with many risk factors still currently unknown.^[1]^

Recently, the incidence rates of post-extubation dysphagia in a large cohort of 933 mixed medical and surgical ICU patients was reported by us in the DYnAMICS study.^[9]^ We revealed the significance of post-extubation dysphagia in the ICU with 12.4% (n = 116/933) of the total ICU population (18.3% of emergency and 4.9% of elective ICU patients) affected. Moreover, 60% of patients leaving the ICU having been identified as dysphagia positive, were still dysphagic at hospital discharge. Furthermore, the presence of dysphagia was associated with increased morbidity (e.g., increased resource use, increased hospital length of stay) and, after adjustment, dysphagia remained an independent predictor for 28-day and 90-day mortality (excess 90-day mortality 9.2%).^[9]^ Diagnosis of post-extubation dysphagia is most commonly established by ICU nurses at the bedside (dysphagia screening) followed by an assessment by a trained speech and language pathologist (SLP) or occupational/ physio-therapist.^[1,17,18]^ Fiberoptic Endoscopic Evaluation of Swallowing (FEES) is an instrumental examination technique that allows visualization of the pharynx during swallowing. Data show that FEES is well tolerated and considered a safe technique^[19–22]^ with minimal complications.^[23]^

Treatment for dysphagia is typically limited to dietary adjustment and postural changes as well as compensatory manoeuvres aiming to improve swallowing function.^[1,17,24]^ The therapeutic efficiency of such ‘traditional’ therapies is limited, with no evidence for clinical benefit in ICU patients.^[1,25]^ Novel interventional approaches to treat dysphagia are therefore warranted. Pharyngeal electrical stimulation (PES) is a novel technique that offers a new treatment option for dysphagic patients and in 2 recent studies, the benefits of PES in severely dysphagic tracheotomized stroke patients^[26,27]^ were demonstrated. In the first study, Suntrup et al^[27]^ conducted a single-center, randomized controlled pilot study in 30 severely dysphagic tracheotomized acute stroke patients. Patients were given PES or sham and thereafter assessed for decannulation readiness using a FEES-based decannulation algorithm.^[28]^ In their study, Suntrup et al^[27]^ found that dysphagia improved enabling decannulation in 15/20 (75%) patients of the treatment group, whereas only 2/10 (20%) of control patients showed spontaneous remission of post-stroke dysphagia sufficient enough to allow for subsequent removal of the tracheal cannula. In the follow-on multi-center, randomized controlled PHAST-TRAC study by Dziewas et al^[26]^ conducted in 69 severely dysphagic tracheotomized stroke, PES was associated with 17/35 (49%) patients being ready for tracheostomy decannulation when compared to just 3/34 (3%) controls. PES is considered to stimulate afferent sensory feedback resulting in enhanced reorganization of the swallow-related motor-cortex, faciliatory activation of cortico-bulbar pathways, and increased salivary substance P levels, a swallow-related neurotransmitter, inducing more quantitative and qualitative swallows.^[1,29–31]^ Moreover, the relationship between PES treatment efficacy and short times to treatment (favoring treatment earlier after stroke, or with a shorter duration of mechanical ventilation) in the PHAST-TRAC study^[26]^ are thought to be related to the development of critical illness dysphagia due to critical illness polyneuropathy and myopathy in patients with prolonged ICU treatment and mechanical ventilation.

We embarked to design a clinical study that evaluates the effectiveness of PES in reducing the severity of unsafe swallows in mixed emergency adult ICU patients with recent extubation following mechanical ventilation.

## Objectives

2

### Primary objective

2.1

To evaluate the effectiveness of PES (Phagenyx) treatment in reducing the severity of unsafe swallows.

### Secondary objectives

2.2

To evaluate and further characterize the effectiveness of PES treatment in improving nutritional management and reducing the severity of dysphagia.To evaluate the effectiveness of PES treatment on general patient health outcomes.

### Other objectives and supplementary data collected

2.3

Exploratory additional analysis of the effectiveness of PES treatment in reducing dysphagia severity and other health outcome measures.

## Methods

3

### Design

3.1

Prospective, multi-center, 1:1 randomized, sham-controlled, patient-masked, outcome assessor-blinded study designed to assess the effects of PES for the treatment of oropharyngeal dysphagia after invasive mechanical ventilation (of any length of time; by means of naso- or oro-tracheal tube) in critically ill intensive care unit (ICU) patients (active study protocol version 1.0, dated Nov 8, 2018). A study flowchart is provided (Fig. 1). Patient randomization will occur after dysphagia severity is classified as ‘aspiration’ (PAS score ≥ 6) on FEES assessment, and the Phagenyx Catheter is successfully placed. Randomization will be on a 1:1 basis at each site stratified for neurological vs non-neurological reason for admission (APACHE IV diagnostic group). All randomized patients will receive either PES treatment or sham (comparator) by a health care professional who is unblinded to the treatment assignment (PES treater). Sham treatment will be performed using the same device without delivering energy. Administration of all protocol-specific assessments, other than PES or sham, will be conducted by study personnel who are blinded to the treatment assignment, including therapists delivering standard dysphagia care (other forms of electrical stimulation treatment for dysphagia are not permitted in this study). FEES assessments of swallowing safety and decisions on patient treatment will be made by the local clinical team responsible for the patient's care. Study data will be collected using an electronic Case Report Form (eCRF) (SYNCRONY, Syntactx Technologies LLC, NY).

**Figure 1 F1:**
[figure not shown]
Study flowchart.

An Independent FEES Review Committee (IFRC), external to the study sites, will be established for analysis of all study-related FEES assessment parameters and to confirm/validate the PAS scoring of the local clinical FEES assessor(s). FEES results will not be scored in duplicate but discrepancies in ratings between the local team and IFRC, or concerns about the quality of submitted records will be reviewed and discussed with the local team for (re-)training purposes only. All FEES records will be coded so that records are only identified by site number, bolus number, patient number, and study visit (i.e., screening or follow-up). The IFRC will be blinded to the treatment assignment as well as the actual treatment received.

Six or more investigational academic hospital sites across Europe are anticipated to participate in this study. Factors considered for site qualification of ICUs include, but are not limited to: potential number of suitable patients, availability, and experience of conducting FEES. The enrolment period is expected to be approximately 48 months from the time of first patient recruitment to the final study visit. Each patient's participation will last for up to 90 days with assessments at the following intervals: screening, baseline, day 2 (approx. 24–60 hours), 7 ± 1 days, 14 ± 1 days or hospital discharge (whichever is first) after completion of the final PES treatment. 30-day and 90-day mortality data will also be collected from the patients (electronic health record) medical notes - this will not require an additional visit but a phone call may be conducted depending on the patient's status. Dysphagic patients enrolled into the study will continue to receive nutrition as deemed appropriate by the ICU team. Patients with a nasogastric feeding tube in place at the time of screening/enrolment will have their nasogastric tube replaced with the Phagenyx Catheter since the Phagenyx Catheter may also be used to deliver nutrition to the patient as required for up to 30 days after placement.

## Study population

4

Up to 400 (360 evaluable) mixed emergency (unplanned) admission adult critically ill ICU patients post invasive mechanical ventilation with confirmed oropharyngeal dysphagia will be recruited in to this study.

## Inclusion and exclusion criteria

5

Pre-screening inclusion criteria (all of the following criteria must apply):

Age ≥18 and ≤85 years,Emergency ICU admission (unplanned admission),Recent extubation following invasive mechanical ventilation (of any duration) by means of endotracheal tube,Presence of post-extubation dysphagia as determined by the participating sites’ standard of care (SOC).

Screening / Enrolment Criteria: To be eligible for enrolment in this study, an individual must meet all of the following additional criteria:

Presence of written informed consent according to respective national guidelines (patients are considered enrolled once informed consent is provided),Dysphagia severity status classified according to PAS on FEES assessment as ‘aspiration’ (PAS score ≥6),Richmond Agitation and Sedation Scale (RASS) score within the range of −1 to +2 *(i.e., if score equals* −*2,* −*3,* −*4 or +3, +4, patient is excluded)*,

Randomization inclusion criteria (post consent): The following additional criteria must be met for randomization:

Successful placement and subjective tolerance of the Phagenyx Catheter within 2 days of extubation.

Exclusion criteria: (any of the following):

Nasal anatomical deformity, nasal airway obstruction; patient who have had recent oral, nasal or oesophageal surgery or patient presenting with facial and/or cranial fractures or any other circumstance (e.g., history of oesophageal perforation, stricture, pouch, resection or rupture) where placement of a standard nasogastric feeding tube would be deemed unsafe,Cardiac or respiratory condition that might render the insertion (placement) of a catheter into the throat unsafe,Presence of a permanently implanted electrical deviceAre pregnant (pregnancy test) or known lactating women,Have non-neurogenic dysphagia (e.g., Cancer-related),Any prior tracheostomy,Patients who at the time of extubation have a treatment limitation, life expectancy, or are moribund, that prevents or would prevent compliance with study-specific instructions or procedures (as judged by the investigator)Severe cognitive impairment or other reasons that prevents compliance with study-specific instructions or procedures (as judged by the investigator),Previous history of dysphagia of any origin,Pre-existing tube feeding of any form (e.g., percutaneous gastric/enteral feeding tube related to previous injuries indicating previous dysphagia. Nasogastric feeding tubes are not an exclusion criterion),Participation in another interventional study (medicinal or device) that could influence the outcomes of PES,Treatment of dysphagia with other forms of electrical stimulation.

## Outcome measures

6

### Primary endpoint

6.1

A composite endpoint using the Finkelstein-Schoenfeld (FS)^[32]^ (win-ratio) statistic, (see statistical considerations) analyzed on a hierarchy, based on clinical priorities, of the following 2 endpoints:

Swallowing safety based on worst PAS score in a series of up to 4 boliousing thin stimuli (water) for each patient as determined by a FEES assessment on day 2 (approx. 24–60 hours) after completion of the final PES treatment, converted to a trichotomized ordinal response of safe (PAS 1–3), penetration (PAS 4–5), or aspiration (PAS 6–8),Dysphagia Outcome and Severity Scale (DOSS) score determined by bedside assessment 7 ± 1 days after completion of the final PES treatment.

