### Secondary endpoints

6.2

1.Changes in nutritional management and severity of dysphagia will be assessed by:Dysphagia status as measured by DOSS at baseline, day 2 (approx. 24–60 hours), 7 ± 1 days and at 14 ± 1 days (or hospital discharge if earlier) after completion of the final PES treatment (to assess changes in functional severity of dysphagia over time),Time (days) from randomization to removal of feeding tube,Time (days) to first oral intake (if applicable. Oral intake is minimally defined as movement from for example FOIS 3 (Tube dependent with consistent intake of liquid or food) to FOIS 4 (Total oral diet of a single consistency) or from DOSS 2 (Moderately severe dysphagia) to DOSS 3 (Moderate dysphagia),Total days of enteral feeding,FOIS scale at baseline, day 2 (approx. 24–60 hours), 7 ± 1 days and at 14 ± 1 days (or hospital discharge if earlier) after completion of the final PES treatment.General health outcomes will be assessed by:Time (days) from extubation to ICU discharge,ICU LOS (Length of stay in ICU),Hospital LOS (Length of stay in hospital)Number of patients with re-intubation during hospital stayMortality.

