### Other endpoints and supplementary data collected

6.3

Additional data for exploratory analysis will be collected in relation to dysphagia severity and general patient outcomes. For changes in severity of dysphagia between FEES assessments, the IFRC will evaluate secretion severity (Murray Secretion Severity Rating Scale (SSS)), bolus residue (Yale Pharyngeal Residue Severity Rating Scale (YRS)) and global dysphagia severity (Global Dysphagia severity Score (GDS). Further, swallowing safety and efficiency will be analyzed using the worst PAS score for each bolus consistency for each patient as determined by a FEES assessment on day 2 (approx. 24–60 hours) after completion of final PES treatment, converted to a dichotomized ordinal response of non-aspirator (PAS 1–5) or aspirator (PAS 6–8) (performed to address presence of aspiration, a key medical problem). General patient health outcome data collected and to be analyzed include time from extubation to hospital discharge (days), days on antimicrobials post-extubation (while in ICU), hospital discharge destination (home, home + care, nursing home, other hospital, rehabilitation center), ICU readmission rate during hospital stay, number of and reason for tracheostomies per group after PES treatment during hospital stay and total number of chest X-rays during hospital stay after ICU discharge for suspected pneumonia. Phagenyx treatment parameters (catheter insertion-related, ease of use, threshold, tolerance and stimulation levels) and nursing workload (TISS-28) data will also be collected.

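### A significant PAS-then-DOSS composite does not by itself show fewer unsafe swallows, and PAS alone has no secondary endpoint

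*Protocol article*

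**What the plan says.** Section 2.1 of the protocol article gives the single primary objective: "To evaluate the effectiveness of PES (Phagenyx) treatment in reducing the severity of unsafe swallows". Section 2.2 places "improving nutritional management and reducing the severity of dysphagia" under the secondary objectives.

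Section 6.1 defines the primary endpoint as a composite "analyzed on a hierarchy, based on clinical priorities, of the following 2 endpoints". The first level is swallowing safety: the worst day-2 thin-liquid PAS, "converted to a trichotomized ordinal response of safe (PAS 1–3), penetration (PAS 4–5), or aspiration (PAS 6–8". The second is the DOSS "score determined by bedside assessment 7 ± 1 days after completion of the final PES treatment". Section 17.1 sends pairs tied on PAS to DOSS and tests one null hypothesis on the overall win probability. It sets no condition on the PAS level.

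The secondary list in section 6.2 opens with "Dysphagia status as measured by DOSS at baseline" and later visits. It continues with feeding, FOIS, length of stay, re-intubation and mortality, and contains no PAS measure. Section 6.3 analyses PAS separately among the exploratory outcomes, per bolus consistency, "converted to a dichotomized ordinal response of non-aspirator (PAS 1–5) or aspirator (PAS 6–8".

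The Discussion (section 18) says the trial will settle whether PES lessens the severity of unsafe swallowing. Its closing sentence is broader and refers to dysphagia severity.

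**The concern.** Within the primary endpoint, only PAS is labelled swallowing safety. DOSS rates functional severity and guides diet and nutrition (section 11.3), which the article treats as a secondary objective. The component that carries the primary objective therefore has no confirmatory or secondary estimate of its own, while the lower-ranked component has one.

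What is at stake is the wording of the conclusion. All patients enter with PAS 6 or more, and the sample-size section assumes that half of controls remain there, so a substantial minority of pairs will tie on PAS and be decided by DOSS. A significant composite could then be reported as meeting the unsafe-swallows objective when the evidence on PAS itself is inconclusive.

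**Working it through.** **Inputs from the article.** One-sided 0.025 (17.4). Control PAS response (to 1–5) 50%, PES 65%, DOSS mean gain 0.7, 100 per arm for at least 90% power, maximum 360 evaluable, 10% loss, 400 recruited (17.2).

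**Assumed, because the article does not give them.** DOSS SD, the PAS–DOSS correlation (0 or 0.5), and the share of PAS 1–5 patients who are safe, PAS 1–3 (0.5 to 0.9). In the simulations DOSS is rounded to 1–7 with a control latent mean of 3.5. The design is treated as fixed, without the interim.

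**The plan's own figures.** 360 / (1 − 0.10) = 400, as stated. With 50% vs 65% and a DOSS shift of 0.7, simulated composite power at 100 per arm is 69–92% over SD 1.25–2.0. The stated 90% is reachable under favourable assumptions but cannot be confirmed from the article. Simulated type I error under the global null is 2.4%.

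**Share of pairs tied on PAS, no PAS effect.**
- Half aspirate; the other half split evenly: 0.50² + 0.25² + 0.25² = 0.375.
- Safe share 0.9: 0.50² + 0.45² + 0.05² = 0.455.

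So about 37–46% of pairs pass to DOSS, and PAS decides the rest.

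**Hand check: no PAS effect, DOSS +0.7, SD 1.5, independent, 50/25/25 split.**
- DOSS win difference in tied pairs: 2Φ(0.7 / (1.5√2)) − 1 = 2Φ(0.33) − 1 ≈ 0.26.
- Net win difference: 0.375 × 0.2586 ≈ 0.097.
- Standard error √((2n + 1) / (3n²)): 0.082 at n = 100, 0.061 at n = 180.
- Chance of significance: Φ(0.097/0.082 − 1.96) ≈ 22%; Φ(0.097/0.061 − 1.96) ≈ 36%.

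Simulation of the same case gives about 21% and 34–35%.

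**Range, no PAS effect, DOSS shift 0.7** (SD 1.5 or 2.0, correlation 0 or 0.5, safe share 0.5–0.9): 15–32% at 100 per arm and 21–52% at 180 per arm. After rounding and truncation the realised DOSS mean difference is about 0.60–0.67. A smaller SD would push the figures up.

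**What these wins look like.** In the hand-check setting, observed PAS favours PES in about 97–99.7% of the significant trials. PAS tested alone is significant in only roughly a tenth of them. The direction of PAS therefore hardly separates these trials from trials with a real PAS effect; its interval does.

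**Dependence of planned power on DOSS.** The planned PAS effect with no DOSS effect gives the composite only about 45–46% power at 100 per arm.

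**PAS response alone, 50% vs 65%** (mean proportion 0.575).
- n = 100: SE under the null √(2 × 0.575 × 0.425 / 100) = 0.0699; under the alternative √((0.25 + 0.2275) / 100) = 0.0691. Power = Φ((0.15 − 1.96 × 0.0699) / 0.0691) ≈ 57%.
- n = 180: about 82%.
- 90% power: (1.96 × 0.6991 + 1.2816 × 0.6910)² / 0.15² ≈ 227 per arm, or 454 evaluable, above the 360 maximum.

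**The case against.** The strongest reply is that PAS has priority and drives the statistic. With a 50/25/25 split it decides 62.5% of pairs, and letting a lower outcome break ties is inherent in any hierarchical composite and openly stated. This stands. A reader might infer that the trial can succeed on DOSS alone, with PAS flat or worse. At the planned DOSS effect the document's figures do not support that as a usual outcome: in the hand-check setting nearly all such wins also show an observed PAS advantage, by chance. Larger DOSS effects could carry the composite further, but the article does not plan for them.

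A reader might also infer that PAS is analysed nowhere else. That is not so. The exploratory analysis in section 6.3 uses the same cut as the sample-size assumption and would show a null or adverse aspiration result. But it is exploratory, and it merges safe swallows with penetration, a distinction the primary endpoint ranks.

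Reporting by level may be in the SAP, which is not shown, so its absence from the article is not the point. The point is how the article assigns objectives and endpoints to tiers.

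Finally, the 180-per-arm figures apply only if the interim adaptation takes the trial to its maximum, and no simulation here models the interim or futility stopping. Both limits stand.

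**Conclusion.** The mismatch is real, and the article fixes it in sections 2.1, 6.1–6.3 and 17.1. The objective is swallowing safety, the test is on a mixture, and the safety component has no endpoint above exploratory rank. A significant composite shows an effect on the PAS/DOSS hierarchy; it does not by itself establish an effect on unsafe swallows. With no true PAS effect and the planned DOSS effect, significance arises in roughly 15–32% of trials at 100 per arm and 21–52% at 180, against a nominal 2.5% when neither outcome is affected. These percentages rest on the assumed DOSS SD, PAS split and correlation and on a fixed design. They show that the issue is not negligible and should not be read as precise. The composite remains a valid test of its own hypothesis. What should change is the rank of PAS alone and the basis for the safety claim.

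**What to change.** List three-level day-2 thin-liquid worst PAS as the first secondary endpoint, estimated as a win difference or common odds ratio with a 95% CI. Beside the composite, show wins, losses and ties separately for the PAS and DOSS levels. Base any conclusion about unsafe swallows on the PAS estimate and its interval, not merely on its direction. If the interval does not support a PAS effect, word the conclusion as an effect on the PAS/DOSS composite. Alternatively, broaden the objective in section 2.1 to include functional dysphagia severity.

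This needs one endpoint line and one sentence on interpretation. It needs no new data, and the primary test and its power are unchanged. PAS should not become a second hurdle for the primary test. The cost is a narrower claim when PAS is inconclusive, which is likely at N = 200 because PAS response alone has only about 57% power there.
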